**Methods/Design:**

This is a school-based cluster-randomized controlled trial. Three intervention and three control (no intervention) full-time public schools were randomly selected in Fortaleza, northeastern Brazil. Students (*n* = 1,272) from classes in Grades 7–9 were eligible, and 1,085 (548 in the intervention and 537 in control schools) completed the baseline and follow-up measures. The program duration was approximately four months and took place in 2014. Intervention strategies focused on teacher training, activities on health in the curriculum, active opportunities in the school environment (the availability of equipment for PA), and health education (health materials for students and parents). Data collection was undertaken before and immediately after the intervention. The primary variables included the practice of PA (weekly PA volume, PA behavior change stage and preference for PA during leisure-time) and screen time (TV and computer/video games). Potential intrapersonal, interpersonal and environmental mediators of PA and screen time were evaluated by a standardized questionnaire. Other lifestyle components (e.g., eating habits, substance use), psychological (e.g., self-rated health, body satisfaction) and biological (general and abdominal obesity) aspects, as well as academic performance were also evaluated in the total sample. Depressive symptoms, eating disorders, sleep quality, objectively-measured PA, and sedentary time were evaluated in obese students.

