## Methods

### Aim and study design

This study was descripted following the Consolidated Standards of Reporting Trials (CONSORT) recommendations (Additional file 1). This is a cluster-randomized controlled trial and the school was the sample selection unit [27]. The primary objective of the *Fortaleça sua Saúde* program was to determine whether a multicomponent program (teacher training and activities on how to discuss health topics in the general curriculum and PE classes, active opportunities in the school environment and health education in the school community) would increase PA practice and reduce screen time among full-time elementary students (Grades 7–9) in Fortaleza, northeastern Brazil. A further primary objective was to identify the effectiveness of the program on intrapersonal, interpersonal and environmental variables related to PA and screen time, and to determine which of these variables mediate active lifestyle changes. The program’s secondary objectives included: (i) to determine whether the program is also effective for different health factors (e.g., nutritional status, health behavior, quality of life, and others); (ii) to identify its effectiveness for addressing eating disorders, sleep quality and objectively-measured PA and sedentary time among obese students; and (iii) to evaluate the program execution, including indicators of the implementation, maintenance, and costs of this program.

The participation of the students involved in this study was authorized by the parent/guardian, by signing the informed consent form. The National Research Ethics System (protocol No. 17366313.9.0000.0121) approved this research project and it follows resolutions 196 and 251 of the National Health Council. Each school will receive a final report containing the program results and practical recommendations for application in schools.

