### Setting and population

Fortaleza is the capital of the state of Ceara, northeastern Brazil, and has a population of 2,452,185 inhabitants (the fifth largest city in Brazil in terms of population) [28]. This municipality has an area of 314 km^2^ and a Human Development Index (HDI) of 0.754 — it is the 19^th^ HDI among the 27 Brazilian state capitals [28]. The city of Fortaleza is geographically divided into six administrative regions [28].

According to the Municipal Education Department, Fortaleza had 464 municipal schools in 2014 (www.sme.fortaleza.ce.gov.br/mapeamentoescolar). Of these, 161 schools included classes from Grades 6–9 (34.7 %) and 165 schools included the PSE (35.5 %). Forty schools included Grades 6–9 and PSE, and six out of these schools had a full-time education model. Approximately 2,500 students were enrolled in these six full-time schools, of which 1,272 were enrolled in classes from Grades 7 to 9 (Fig. 1).

Grade six classes were substantially composed of students aged 10 and 11 years old. Based on a validation of the study’s instruments, students from the 6^th^ Grade would have difficulty reporting reliable information. Additionally, age groups considered appropriate by the World Health Organization (WHO) for studies on health behaviors are primarily 13–15 year olds [6–8] and these would be included in successive series, therefore, 6^th^ Grade students were not included.

Thus, all six full-time schools with PSE were eligible. Three schools were in the intervention condition and three additional schools received no intervention (control). The inclusion criteria were students of both genders, aged 12–15 years who were enrolled in Grades 7–9, attending full-time public schools in Fortaleza, northeastern Brazil (Fig. 1).

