### Recruitment of schools and students

The six schools had similar characteristics (e.g., size, target audience, curriculum, etc.) and were located in different administrative regions (geographically dispersed). Therefore, we did not perform peers of schools during random selection.

After authorization of the study by the Municipal Education Department, all directors of eligible schools were informed about the study and the participation criteria. All directors agreed to participate without being informed which treatment group the schools would be assigned to in the study. Thus, we performed the random selection of three schools to each condition (intervention or control). Schools were visited to explain the objectives of the study and the program logistics during the semester. The neighborhood-HDI [28] where the six schools were located was similar between groups (neighborhood-HDIs of 0.215, 0.341 and 0.443 for intervention schools, and 0.170, 0.377 and 0.491 for control schools).

Of the 1,272 eligible students (639 in intervention and 633 in control schools), 1,182 students filled out the baseline measures (92.0 % and 93.8 % of eligible students from intervention and control schools, respectively). The main reason for non-participation at baseline was being absent from school on data collection days. Post-intervention data collection included 1,085 students (response rate of 93.2 % and 90.4 % in intervention and control schools, respectively). Dropping out of school was the main reason for non-participation in post-intervention data collection (Fig. 1).

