Because the data have a multilevel structure (i.e., individuals are clustered within a school), the individual respondents may not necessarily be independent within each school. To correct this, the procedure for complex samples in Mplus will be used in relation to the school. Finally, the results will be reported in accordance with the Consolidated Standards of Reporting Trials (CONSORT) [56].

Statistical procedures proposed by MacKinnon and Dwyer [57] will be considered to identify the effectiveness of the program according to the primary variables and mediating variables, as a common method of intervention study on PA and screen time [13, 15]. Initially, changes in the primary variable (e.g., changes in weekly PA time) will be considered in a regression under the influence of the independent variable (intervention group). In the second model, the mediating variables will also be included in the regression model. Thus, the value of the mediated effect will be calculated by the difference coefficient of the independent variable between the two models [57]. The measure of effect will be expressed in standardized scores (beta) or as an odds ratio, depending on the nature and manner of treatment of the primary variables.

Regression models will also be built in order to identify the effectiveness of the program on secondary variables (e.g., body image, eating habits). The effectiveness of the program on variables among obese students will be analyzed separately using the same statistical procedures. The implementation and economic evaluation will be qualitatively and quantitatively analyzed, considering the different indicators of the evaluation of PA interventions [32]. All analyses will be built using the Mplus program and will be adjusted for possible confounding variables (behaviors at baseline and control variables). The level of significance for the study will be 5 % for two-tailed tests.

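### With six schools and no stated small-sample correction, the planned complex-samples correction does not hold the test of the programme effect at 5%; under the usual defaults its type I error is about 15–19%

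*Protocol article*

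**What the plan says.** All references are to the protocol article.

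- **Design.** The Abstract reports: "Three intervention and three control (no intervention) full-time public schools were randomly selected in Fortaleza". Aim and study design confirms the unit: "This is a cluster-randomized controlled trial and the school was the sample selection unit". Setting and population shows that no further schools existed: "Thus, all six full-time schools with PSE were eligible". Recruitment of schools and students adds that there was no pairing: "Therefore, we did not perform peers of schools during random selection".
- **Clustering.** Statistical considerations accepts that students within a school may not be independent, then says: "To correct this, the procedure for complex samples in Mplus will be used in relation to the school".
- **Error level.** The same section ends: "The level of significance for the study will be 5 % for two-tailed tests".
- **Scope.** That section assigns all analyses to Mplus. These cover the primary variables, the mediators, the secondary variables and the obese subsample.

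The article mentions no finite-cluster factor, no t reference with between-school degrees of freedom, no school-level analysis and no random school effect.

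**The concern.** A cluster-robust variance is justified as the number of clusters grows, and the number of students per cluster does not substitute for it. The programme is a school-level exposure. With three schools against three, unpaired, the contrast rests on six school results and has 6 − 2 = 4 degrees of freedom, even with 1,085 students measured.

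Two things then go wrong in the same direction. The robust variance is too small on average, and a normal critical value of 1.96 is used where t on 4 degrees of freedom requires 2.776. A chance difference among six schools would be called a programme effect about three to four times as often as the stated 5%. Both the Abstract and the Discussion look to the results to guide public policy. The Discussion's list of weaknesses does not mention the small number of schools.

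**Working it through.** **Inputs from the article.** Six schools, 3 v 3, unpaired; 1,085 students at follow-up (548 and 537), about 1,085/6 ≈ 181 per school; two-sided 5%.

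**Assumptions, because the article does not give them.** Default cluster-robust (sandwich) variance; normal reference; either no finite-cluster factor or C/(C−1) = 6/5. Intraclass correlation (ICC) from 0.001 to 0.10, and a 30% rate for binary outcomes. School sizes either equal (181) or unequal (110 to 248).

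**The plan's own figure.** The stated 5% is P(|Z| > 1.96) for a standard normal Z. It is reached when the variance is unbiased and estimated from many clusters.

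**Step 1: bias of the variance.** With k equal schools per arm, the robust variance of an arm mean is Σ(school mean − arm mean)²/k². Its expectation is (k−1)/k times the true value. For k = 3 the factor is 2/3, and with the 6/5 correction it is 2/3 × 6/5 = 0.8.

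**Step 2: link to t.** Let SS be the within-arm sum of squares of the six school means. The robust variance of the difference is SS/9. The ordinary two-sample variance is (SS/4) × (1/3 + 1/3) = SS/6. So the Wald statistic equals t(4)/√(2/3), and the plan rejects when |t(4)| > 1.96 × √(factor).

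| Variance used | Threshold on the t(4) scale | Type I error | Coverage of 95% CI | Correct width / planned width |
|---|---|---|---|---|
| No factor | 1.96 × √(2/3) = 1.600 | 18.5% | 81.5% | 2.776/1.600 = 1.73 |
| Factor 6/5 | 1.96 × √0.8 = 1.753 | 15.4% | 84.6% | 2.776/1.753 = 1.58 |
| Unbiased | 1.96 | 12.2% | 87.8% | 2.776/1.96 = 1.42 |

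With equal schools and normally distributed school means these are exact and do not involve the ICC.

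**Step 3: simulation under no effect.** 10,000 runs per setting, continuous and logistic outcomes, ICC 0.001 to 0.10; the four-covariate setting used 2,000 runs, a continuous outcome and ICC 0.01 and 0.05.

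| Setting | No factor | Factor 6/5 |
|---|---|---|
| Equal schools | 18.0–19.2% | 14.9–16.2% |
| Unequal schools | 19.5–21.8% | 16.3–18.8% |
| Four covariates, equal or unequal schools | 19.2–21.3% | 15.6–18.0% |

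The 6/5 factor combined with a t(4) reference still gave 6.5–8.7%. A t-test on the six school means with 4 degrees of freedom gave 4.5–5.7%.

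**Step 4: permutation test.** There are C(6,3) = 20 allocations, so the smallest possible two-sided p-value is 2/20 = 0.10.

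**The case against.** The strongest reply is that the article names a procedure without specifying its estimator, finite-cluster factor or reference distribution, and that a fuller plan may supply a correction. That stands in part: 15–19% depends on stated assumptions and is not a figure in the document. It does not remove the point, because the article itself fixes the correction, the clustering unit, the software and the error level. The favourable variants in the working still miss 5%: 12.2% with an unbiased variance and a normal reference, and 6.5–8.7% with the 6/5 factor and t(4).

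A second reply is that six schools are a design constraint. This is also true. All eligible schools were used and data collection ended in 2014. A change of analysis restores the error rate but cannot restore power.

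Two stronger readings are tempting and are not supported.

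- A reader might infer that every mediation test is inflated three to four times. The calculation concerns the programme contrast only. The mediator–outcome coefficient draws on within-school variation. A check of it (six schools of 181, ICC 0.0055 to 0.05, 4,000 runs) gave 13–16% with no factor and 11–13% with 6/5: inflated, but generally by less. The article names no significance test for the mediated effect itself, so no error rate can be attached to it.
- A reader might infer that six schools make the covariance matrix singular and the models unusable, given 8 physical activity and 9 screen-time scales. The rank limit of 5 blocks only joint tests of more than five parameters. The article describes no such test, and nothing says that all 17 scales enter one model. The one-degree-of-freedom programme test does not need full rank.

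**Conclusion.** The point holds for the test and interval of the programme effect. Followed as written, with a default cluster-robust variance, a normal reference and no small-sample correction, the plan delivers about 15–19% type I error in place of 5%. Markedly unequal school sizes could take it to about 22%. The missing ICC does not weaken the conclusion, since the result hardly depends on it. Nominal 95% intervals would cover about 82–85%, and correct t(4) intervals are about 1.6 to 1.7 times as wide. If the procedure actually used has a correction that the article does not state, the excess is smaller, and that correction should be written down. This should be settled before the programme effects are reported.

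**What to change.** Replace the clustering sentence in Statistical considerations with wording to this effect:

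> The programme effect on each outcome and each mediator will be tested, and its 95% confidence interval formed, by a two-stage analysis with the school as unit. Stage one fits the student-level covariates without the programme term. Stage two compares the six school summaries by t on 4 degrees of freedom. The summaries are mean residuals for continuous outcomes, and log-odds or the equivalent adjusted residuals for binary outcomes. Results from the Mplus complex-samples procedure, including mediated effects, are exploratory and carry no claim of 5% error control.

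For continuous outcomes, a mixed model with a random school intercept and Kenward–Roger or Satterthwaite degrees of freedom is an acceptable alternative. It was not simulated here, and it does not serve the odds-ratio outcomes.

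**Cost.** The coding is small and uses data already collected. The statistical cost is large: significance now needs an estimate 2.776 standard errors from zero in place of 1.96, and extra students per school cannot make up for missing schools. Three further statements must follow:

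- The 80% power in Statistical considerations and the Discussion's claim of sufficient power must be requalified for 4 degrees of freedom.
- Six schools should be listed among the weaknesses, with the note that a 3 v 3 permutation test cannot go below two-sided p = 0.10.
- Mediation, which Aim and study design makes a further primary objective, should be described as exploratory.

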	√ Daily time using computer/video games on weekdays and weekends days (ICC = 0.80 and 0.75)	
	√ Reducing TV watching-related behavior change stage (ICC = 0.80)	
	√ Reducing computer/videogames using-related behavior change stage (ICC = 0.78)	
Potential reducing screen time mediators	√ *Intrapersonal:* attitude, self-efficacy and expectations (risks/benefits) (α range = 0.64–0.85)	
	√ *Interpersonal:* family modelling, support and norms (α range = 0.56–0.78)	
	√ *Environmental:* family and school environment, house and bedroom characteristics (α range = 0.73–0.85)	
Secondary variables^a^	√ Body mass index	√ Self-rated health (ICC = 0.90)
	√ Waist circumference	√ Stress perception (ICC = 0.79)
	√ Eating habits (ICC range = 0.71-0.89)	√ Body image (ICC = 0.85)
	√ Alcohol use (ICC = 0.71)	√ Sleep quality and duration (ICC range = 0.59-0.75)
	√ Tobacco use (ICC = 0.99)	√ Sleepiness (α = 0.62)
	√ Condom use (ICC = 0.98)	√ Academic performance
	√ Quality of life (ICC = 0.78)	√ School attendance
Descriptive variables^a^	√ Age (ICC = 0.99)	√ Mother’s schooling (ICC = 0.92)
	√ Gender (Kappa = 1.00)	√ Student’s occupational status (Kappa = 0.90)
	√ Father’s schooling (ICC = 0.86)	√ Family’s economy class (ICC = 0.93)
Subsample (obese) Variables^a^	√ Depressive symptoms (α = 0.90)	√ Objectively-measured PA
	√ Eating disorders (α = 0.80)	√ Objectively-measured sedentary time
	√ Sleep quality (α = 0.83)	
Evaluation variables	√ Interest of the school community for the program proposal (before baseline)	
	√ Visibility of the program during implementation (during the program)	
	√ Execution process of the strategies (during the program)	
	√ Interest in keeping the strategies in the future (immediately after the end of the program)	
	√ Maintenance of the program strategies (six months after the end of the program)	
	√ Start-up and operational costs (economic evaluation)	

*PA* Physical activity

^a^All these variables will be measured at baseline and immediately after the intervention

^b^Reliability of the self-reported measures were evaluated using Kappa’s index for dichotomous variables (e.g., gender), intra-class correlation coefficient for ordinal variables (e.g., economic class) and Cronbach’s alpha for scales (e.g., attitude scales). This measures were obtained using a sample (*n* = 194) of students who were not enrolled in the *Fortaleça sua Saúde* program

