### Control and descriptive variables

Potential confounders were measured and included in the data analyses (Table 2). Students’ occupational status (working; not working) was measured [36]. Economic class and parents’ schooling were evaluated with the questionnaire of the Brazilian Association of Research Companies [54]. This instrument groups subjects into economic classes (A1 [richest], A2, B1, B2, C1, C2, D, and E [poorest]) based on a score combining ownership of assets, parents’ schooling and number of employees in the household.

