### Statistical considerations

All sample size power calculations considered a statistical power of 80 % and a 5 % significance level for two-tailed tests. An odds ratio of two [35] was considered, that is, an odds ratio of two students from the intervention group becoming active after the program compared to their peers from the control group (www.openepi.com). Therefore, we estimated a sample of 480 subjects (1:1 between intervention and control groups). A cluster sample selection procedure can involve biases [35] and we, therefore, decided to duplicate the study sample for 960 schoolchildren. Additionally, considering a margin of 20 % for possible losses and refusals, ~1,200 students would be a sufficient sample size to detect a moderate-sized effect with 0.80 of power.

Moderate mediated effect sizes (structural equation models) of the intervention on the primary outcomes were expected (effect size of 0.30). We considered approximately 70 observed variables and the development of up to ten latent variables, considering the number of items included in the PA and screen time questionnaires. Thus, the recommended minimum sample size was 400 adolescents (www.danielsoper.com/statcal); a doubled sample due to the cluster sample selection procedure [35] and an anticipated 20 % dropout rate during the intervention estimating a sample of 960 students. Hence, ~1,200 students would be a sufficient sample size to detect a moderate-sized effect with 0.80 of power for the mediating variables.

We will test whether randomization resulted in a balanced distribution of variables between control vs. intervention students, as well as participating vs. dropout students. The variables that have differing distributions between the two groups will be entered as confounders in all models that test the effectiveness of the *Fortaleça sua Saúde* program.

The effect of the *Fortaleça sua Saúde* program on the primary variables will be tested in accordance with the intention-to-treat principle and in a completers-only framework using Mplus [55]. Intention-to-treat and completers-only analyses will be performed in order to identify the effect of the intervention condition in comparison to the control condition.

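### A mediator's own baseline score is not in the stated adjustment set, although effect on the mediators is a primary objective; it enters only if a balance test flags it

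*Protocol article*

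**What the plan says.** Under Aim and study design, the article states: "A further primary objective was to identify the effectiveness of the program on intrapersonal, interpersonal and environmental variables related to PA and screen time". Table 2 lists the mediator scales under its primary variables, and footnote a says: "All these variables will be measured at baseline and immediately after the intervention".

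Statistical considerations then gives one adjustment rule for every analysis: models "will be adjusted for possible confounding variables (behaviors at baseline and control variables"). The section Control and descriptive variables says "Potential confounders were measured and included in the data analyses (Table 2") and describes occupational status, economic class and parents' schooling. Table 2 adds age and gender. No mediator score is among them.

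A second, data-dependent rule stands in Statistical considerations: "The variables that have differing distributions between the two groups will be entered as confounders in all models that test the effectiveness" of the programme.

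For mediation, "changes in the primary variable (e.g., changes in weekly PA time) will be considered in a regression" on study group. Then "In the second model, the mediating variables will also be included in the regression model", and "the value of the mediated effect will be calculated by the difference coefficient of the independent variable between the two models". No baseline mediator term is named. Whether a mediator is taken as a change or as a follow-up score is not stated.

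**The concern.** Physical activity and screen time are behaviours, so their own baselines are fixed covariates. Attitude, self-efficacy, expectations, support, norms and perceived environment are not behaviours. The article keeps them apart from the behaviours in Table 2 and in the mediation text. Read as written, these primary variables therefore have no fixed adjustment for their own starting level, although the scores will be in the data set.

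Two things are at stake. The first is precision on a primary question. The second is chance imbalance: with three schools per arm, the arms can differ on a mediator before the programme starts. Part of that difference then appears in the estimated effect on the mediator, and from there in the fall of the group coefficient that is read as mediation. Non-behaviour secondary outcomes such as body mass index, waist circumference, quality of life and body image fall outside the stated set in the same way.

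**Working it through.** The plan has no figure of its own to reproduce on this point. Its 80% power and its effect size of 0.30 belong to the sample-size calculation for mediated effects in structural equation models, not to an arm difference in a mediator.

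**Inputs from the article:** six schools, three per arm; 1,085 students with follow-up, so m = 1,085/6 ≈ 181 per school; two-sided 5% level.

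**Assumptions (not in the article):** school ICC of the mediators 0.005 to 0.02; baseline to follow-up correlation rho, shown at 0.6; equal variances at the two times. For the scales the article gives only Cronbach's alpha, which is not rho.

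**1. Chance baseline difference between arms, in SD units.** SD = sqrt[(2/3) × (ICC + (1 − ICC)/m)].
- ICC 0.005: sqrt[(2/3) × 0.01050] = 0.084
- ICC 0.01: sqrt[(2/3) × 0.01548] = 0.102
- ICC 0.02: sqrt[(2/3) × 0.02542] = 0.130

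**2. How much reaches the estimate.** If the same slope rho holds within and between schools, a baseline difference D leads to an expected follow-up difference of rho × D with no programme effect. A follow-up-only model carries rho × D; a change score carries −(1 − rho) × D. For a D of one SD from step 1, at rho 0.6:

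| ICC | follow-up only | change score |
|---|---|---|
| 0.005 | 0.050 | −0.033 |
| 0.01 | 0.061 | −0.041 |
| 0.02 | 0.078 | −0.052 |

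In a linear model the fall in the group coefficient equals the arm difference in the mediator times the mediator's slope on behaviour. With an assumed standardised slope of 0.3, the follow-up-only figures at ICC 0.01 and 0.02 add 0.3 × 0.061 = 0.018 and 0.3 × 0.078 = 0.023 SD to the mediated effect.

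**3. What the balance rule catches.** The form of the test is not stated. A student-level 5% test flags differences above 1.96 × sqrt(4/1,085) = 0.119 SD. That happens in about 24% of randomisations at ICC 0.01 and 36% at ICC 0.02. A test that allowed properly for schools would flag about 5%, by construction.

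**4. Precision.** Adjusting for the baseline score multiplies variance by 1 − rho² against follow-up only, and by (1 − rho²)/[2(1 − rho)] = (1 + rho)/2 against a change score. At rho 0.6 these are 0.64 and 0.80.

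Illustrative power for an assumed arm difference of 0.30 SD in a mediator, noncentral t on 4 df, rho 0.6:

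| ICC | follow-up only | adjusted, only within-school variance reduced | adjusted, school variance reduced equally |
|---|---|---|---|
| 0.01 | 61% | 66% | 79% |
| 0.02 | 42% | 45% | 59% |

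Against a change score, with school variance behaving equally, power goes from 70% to 79% at ICC 0.01 and from 50% to 59% at ICC 0.02.

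**The case against.** **Baseline mediators are not shut out.** A reader might infer that they can never enter. The article does not support that: the balance rule covers any variable that differs between arms, and it catches the largest imbalances. This stands as a limit on the point. But the rule makes the covariates depend on the data, lets smaller differences through, and gains no precision when nothing is flagged.

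**A follow-up-only mediator model is not stated.** The mediation text models changes in the primary variable, and Table 2 puts mediators among the primary variables, so change scores are a fair reading. The baseline is then already subtracted. This also stands. What remains is regression to the mean, with bias in the opposite direction, and a smaller loss of precision.

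**Larger numbers are tempting but unsupported.** A reader might start from the stated 80% power and conclude that adjustment lifts it above 90%, or set the baseline imbalance of 0.08 to 0.13 SD directly against 0.30. The 80% and the 0.30 concern mediated effects. The imbalance is not itself the bias. The gain also depends on how much school-level variance the baseline score explains, and on what baseline behaviours and control variables explain already.

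**An article is shorthand.** Model-by-model detail may well lie in a fuller plan, and silence on change versus follow-up scores is not itself a fault. The covariate set, however, is stated and applied to all analyses; the point concerns what it states.

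**Conclusion.** The point holds in a limited form. For the mediators, a primary objective, the fixed adjustment set leaves out the one covariate likely to matter most, and the balance rule is only a partial substitute.

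The direction is clear under either form of the mediator: adjustment for its baseline removes the carried-over imbalance, under the equal-slope assumption, and does not raise the variance in any scenario worked here. The size is conditional. At rho 0.6, a typical carried-over imbalance is 0.05 to 0.08 SD for follow-up scores and 0.03 to 0.05 SD for change scores, over ICC 0.005 to 0.02. At ICC 0.01 to 0.02 the power gain over a follow-up-only model runs from 3 to 5 points up to 17 to 18 points. Rho, ICC and the 0.30 SD difference are assumptions, and existing covariates would shrink the gain by an unknown amount. Nothing here shows that the mediator results would be invalid; they would be less precise and more exposed to chance than they need be.

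**What to change.** In Statistical considerations, change the parenthesis to: *(behaviors at baseline, the baseline value of the outcome being analysed, and control variables)*. State that this applies whatever the balance test shows, to the mediators and to secondary and obese-subsample outcomes that have a baseline measure. The baseline value is added to the present set; it should not displace baseline behaviours, which the plan already has in these models.

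For the mediation models, add that the baseline score of each mediator entered in a given model is included in that model. Limiting this to the mediators actually entered keeps the covariate list short.

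The cost is a sentence or two of wording and no new data or students. The small downsides are that missing baseline scale scores need handling, and that there are some more student-level covariates in an analysis resting on six schools.
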